## Abstract

**Background::**

To our knowledge, only 1 study with limited sample size tried to evaluate the synergistic effects of ultrasound and low-level laser therapy (LLLT) in patients with knee osteoarthritis. Further research is needed to confirm this synergy with larger numbers and better design. Therefore, we will conduct this present randomized double-blind study to evaluate the synergistic effects of simultaneously applying ultrasound plus LLLT on pain and muscle function in patients with knee osteoarthritis.

**Methods::**

The study protocol is a randomized, controlled, double-blind design. The study will be conducted at our academic hospital from February 2021 to January 2022. The study protocol was approved through Institutional Review Board in the Hunan Provincial People's Hospital. Patients will be assigned at random to the ultrasound + LLLT group, LLLT group, or the ultrasound group. After baseline examination, all patients will be given a full explanation of the treatment protocol and will be required to sign a written informed consent for study participation and for publication of the results. All the data collectors, surgeons, statistical analysts, as well as result assessors are not aware of grouping assignment. The primary outcome is weekly change in pain intensity relative to baseline through 6 weeks of therapy.

**Results::**

This protocol will provide a reliable theoretical basis for the following research.

**Conclusion::**

It is assumed that there will be a remarkable difference in postoperative outcomes between the intervention and control groups.

**Trial registration::**

This study protocol was registered in Research Registry (researchregistry6470).

## Introduction

1

Osteoarthritis of the knee is a degenerative inflammatory disease that affects the entire joint and is characterized by progressive loss of cartilage with pain, disability, and decreased quality of life. The disease occurs when the dynamic equilibrium between deterioration and restoration becomes unbalanced, often in situations where the mechanical stress applied is greater than the one that can be supported by the joint tissues.^[1]^ Increased inflammatory activity is associated with higher pain intensity and faster disease progression in osteoarthritis.^[2]^

There are still no disease-modifying treatments for knee osteoarthritis. Currently, available options include palliative pharmacological and nonpharmacological modalities. The core goals of these therapies are to reduce joint pain, improve joint function, and achieve a better quality of life.^[3,4]^ Though nonsteroidal anti-inflammatory drugs are widely used to treat these patients, their side effects, particularly the high incidence of side effects in the upper gastrointestinal tract, limit their use. As a result, many physical therapy agents have been introduced, such as ultrasound, electrical stimulation, intensive exercise, and thermal therapy.^[5]^

Physical therapy is designed to reduce pain, improve function or quality of life, reduce the burden on the joint, promote adaptability to certain activities, prevent deformities and slow the progression of the disease. Jamtvedt et al performed a systematic review related to physical therapy for knee osteoarthritis and found that only exercise and weight loss were effective in improving pain and function.^[6]^ Acupuncture, percutaneous electrical nerve stimulation, and low-level laser therapy (LLLT) had moderate quality of evidence for the same variables. The quality of evidence for other interventions was low or nonexistent.^[7]^

Various studies have shown that LLLT has a positive therapeutic effect in treatment of knee osteoarthritis for rats, rabbits and clinical trials of humans.^[8–10]^ In parallel, therapeutic ultrasound has also shown positive effects for the treatment of knee osteoarthritis, both in vitro models and in vivo studies on animals and humans.^[11,12]^ The main positive effects of these modalities are, for example, anabolic effects on cartilage, anti-inflammatory effects, analgesia associated with muscle relaxation and improvements in microcirculation.

To our knowledge, only Paolillo et al tried to evaluate the synergistic effects of ultrasound and LLLT in patients with knee osteoarthritis. However, the sample size of their study was too small to draw convincing conclusions, thus further research is needed to confirm the synergies.^[13]^ Therefore, we will conduct this present randomized double-blind study to evaluate the synergistic effects of simultaneously applying ultrasound plus LLLT on pain and muscle function in patients with knee osteoarthritis. It is assumed that there will be a remarkable difference in postoperative outcomes between the intervention and control groups.

## Materials and methods

2

### Participants

2.1

Subjects will be included in this study if they

1.have painful knee osteoarthritis for at least 6 months with degenerative osteoarthritic knee of grade 2 to 3 or less based on radiographic diagnosis in the Kellgren and Lawrence grading of osteoarthritis,2.have no limitation of range of motion (ROM) except for minimum tightness in the knee joint,3.do not engage in any high-joint-loading exercises such as hiking or tennis playing and have not undergone any specific treatments 3 months before entering the study,4.have a minimum score of 25 on the Western Ontario and McMaster Universities Osteoarthritis Index (WOMAC) total score, and5.have a knee pain ≥4 on the visual analog scale (VAS) in the previous 3 months.

Subjects will be excluded from the study at pretreatment evaluation if they have any other musculoskeletal problems associated with the knee joint, such as fracture, tendon or ligament tears, meniscus injury, rheumatoid arthritis, or knee surgery. Patients will be also excluded if they have musculoskeletal problems associated with the hip or ankle/foot joints, have central or peripheral neuropathy, or have received physical therapy and/or intra-articular corticosteroid or hyaluronic acid injections during the last 6 months.

### Study design

2.2

The study protocol is a randomized, controlled, double-blind design. The study will be conducted at our academic hospital from February 2021 to January 2022. The study protocol was approved through Institutional Review Board in the Hunan Provincial People's Hospital (HN20201208) and was registered in the research registry (with number: researchregistry6470).

### Random allocation

2.3

Before starting the study, a randomization list is produced using software-generated randomized numbers; the randomization depends on random blocks of 10 (Table 1). Patients will not know to which group they are assigned or which treatment they will be offered. Patients will be assigned at random to the ultrasound + LLLT group, LLLT group, or the ultrasound group. Participants are enrolled by the research assistant. After baseline examination, all patients will be given a full explanation of the treatment protocol and will be required to sign a written informed consent for study participation and for publication of the results. All the data collectors, surgeons, statistical analysts, as well as result assessors are not aware of grouping assignment (Fig. 1).

**Table 1 T1:** Patient baseline demographics.

Demographics	Combined group	LLLT group	Ultrasound group	*P* value
Number of patients (knees)				
Age at surgery^∗^ (years)				
Male sex (no. [%])				
BMI^∗^ (kg/m^2^)				
Right side (no. [%])				
Follow-up^∗^ (years)				

BMI = body mass index, LLLT = low-level laser therapy.

∗ The values are given as the mean and the SD.

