### Intervention protocol

2.4

The interventions will be carried out twice a week for 2 months, for a total of 15 sessions, and will be performed by 2 experienced physiotherapists who are not evaluators, maintaining the blind nature of the method. For LLLT, the volunteers will be treated with low-level laser (Endolaser 476, Enraf Nonius, Rotterdam, The Netherlands), wavelength of 808 nm, 0.028 cm^2^ spot area, 100-mW power output, fluence of 200 J/cm^2^, energy per point of 5.6 J, in the regions of the lateral and medial epicondyle of tibia and femur, in the joint line of the lateral and medial knee, and the popliteal fossa (tendon of the biceps femoris, semitendinosus and between the tendons) and on the patellar tendon region, totaling 10 isolated points, for 56 seconds per point, total energy of 56 J. US will be applied using an aqueous gel as a coupling medium in circular movements with the probe at right angles. The treatment area is 25 cm^2^ and extends to both patellofemoral and tibiofemoral borders of the target knee on both the lateral and medial margins, avoiding the patella. Continuous ultrasonic waves with 1 MHZ frequency and 1 watt/cm^2^ power are applied with a 4-cm diameter applicator (Petson.250 ultrasound equipment Petas, Turkey) for 5 minutes in each session. To avoid the immediate effects of heat application, the outcome data evaluation is performed 2 days after completion of the last session.

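### One published block length of 10, with the enroller not named as unaware of allocation, makes about 7% to 13% of assignments certain if past assignments can be learnt

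*Protocol article*

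**What the plan says.** Section 2.3 (Random allocation) describes a software-generated list and states that "the randomization depends on random blocks of 10". No other block length, no strata and no block composition are given. The list serves three arms: "Patients will be assigned at random to the ultrasound + LLLT group, LLLT group, or the ultrasound group". There is one site: "The study will be conducted at our academic hospital from February 2021 to January 2022".

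On who knows what, Section 2.3 says of patients that "Patients will not know to which group they are assigned or which treatment they will be offered". Of staff it says "All the data collectors, surgeons, statistical analysts, as well as result assessors are not aware of grouping assignment". The person who recruits is identified separately: "Participants are enrolled by the research assistant". That role does not appear in the list of those unaware.

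Section 2.4 (Intervention protocol) says that treatment "will be performed by 2 experienced physiotherapists who are not evaluators, maintaining the blind nature of the method". It describes laser applied at 10 separate points and ultrasound given with gel and a moving probe, and mentions no sham device. Section 2.7 sets the total at 120 subjects.

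**The concern.** In a permuted block of known length, each assignment already made narrows what is left. Someone who knows the length and has counted the earlier assignments can sometimes state the next one with certainty, mostly at the end of the block. Three features make this more relevant here: the length is printed in the protocol, all patients come through one hospital on what appears to be one list, and the treatments can be told apart by anyone who sees them given.

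If the enroller could foresee an arm, a patient could be deferred or steered. Some room for this exists in Section 2.1, chiefly in judging whether tightness of the knee is minimal. The primary outcome is patient-rated pain, and Section 2.7 plans an unadjusted Kruskal–Wallis comparison, which cannot remove selection of this kind. Changing only to a fixed length that divides by three would not cure the problem.

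**Working it through.** **Inputs.** Block length 10 and three arms (Section 2.3); 120 subjects (Section 2.7), hence 120/10 = 12 blocks. Equal allocation is assumed, since no ratio is stated. As 10 = 3×3 + 1, a block cannot be balanced, and the nearest composition is 4:3:3. The plan gives no predictability figure to reproduce. All cases below assume that every earlier assignment is seen.

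**Case A: known 4:3:3 (the enroller knows which arm has four).** An assignment is certain when only one arm remains in the block. The expected number per block is the sum over k of the probability that the last k slots are all the same arm:
- k = 1: 1
- k = 2: (4×3 + 3×2 + 3×2)/(10×9) = 24/90 = 0.267
- k = 3: (24 + 6 + 6)/(10×9×8) = 36/720 = 0.050
- k = 4: 24/(10×9×8×7) = 24/5040 = 0.005

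The sum is 1.321 per block, or 13.2% of assignments. Over 12 blocks this is 12 × 1.321 = 15.9, about 16 of 120. Simulation gives 13.2% to 13.3% certain and a best-guess success of about 54%, against 33.3% by chance.

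**Case B: the arm with the extra slot varies and is unknown.**
- Slot 10 is unresolved only if the first nine run 3:3:3, that is, if the last slot belongs to the arm with four: probability 4/10. It is therefore certain in 60% of blocks (simulated 60.3%).
- Slot 9 is certain only if the first eight run 4:3:1: 2×(3×2)/90 = 0.133.
- Slot 8 is certain only if the first seven run 4:3:0: 2×6/720 = 0.017.

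The sum is 0.75 per block, or 7.5% of assignments; 12 × 0.75 = 9 of 120. Simulation gives 7.4% to 7.5% certain and about 49% correct best guesses.

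**Case C: a fixed, known block of 9 (3:3:3).** 1 + 18/72 + 18/504 = 1.286 per block; 1.286/9 = 14.3% certain. Simulated best guessing is 53.2%. Divisibility by three alone therefore does not help.

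**Case D: sizes drawn at random from 6, 9 and 12.** Suppose the enroller knows this set but not the size of any given block. Updating the probabilities after each assignment in simulation gives 2.4% certain (120 × 0.024 = about 3) and a best-guess success of 52.6%.

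**No past assignments seen.** Under a known 4:3:3, always naming the arm with four is right 4/10 = 40% of the time, and nothing is certain.

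**Is there opportunity to observe?** If 120 patients enrolled evenly over the 12 months of the study, that would be 10 a month, so a block would fill in about a month. Section 2.4 spreads treatment over two months. Earlier members of a block would usually still be attending when its last patient enrols. This makes observation possible; it does not show that it occurs.

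**The case against.** The strongest reply is that nothing in the article says the research assistant sees treatments or learns assignments. The trial is described as double-blind, and treatment is given by two physiotherapists who do not evaluate. Not being named as unaware is different from being aware, and the assistant may be one of the data collectors, who are named. This stands, and for that reason the point is conditional. A reader might infer that past treatments are in fact visible to the enroller; the documents do not support that as a fact.

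A reader might also infer that the end of every block can be predicted. That holds only under a known, fixed 4:3:3, which the article does not state. If the extra slot varies, the last assignment is certain in about 60% of blocks.

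Third, who holds the list and when each assignment is released are details that a journal article commonly leaves to the full protocol. Their absence is not charged here. If such safeguards keep past assignments from the enroller, the predictability largely disappears.

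Fourth, varying the block size barely changes best guessing: 52.6% against 54.0% in Case A (1.4 points lower) and 48.7% in Case B (3.9 points higher). That is correct. The gain is in certainty only, from 7% to 13% down to about 2%.

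Finally, a fixed block length is a legitimate design, and most eligibility criteria are numeric or radiographic, which limits the room for steering. Both statements are fair. What remains is that a disclosed fixed length was chosen where an undisclosed varying one costs almost nothing.

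**Conclusion.** The point holds as a conditional weakness in a stated method. The article fixes and publishes one block length at a single site, for treatments that look different, and does not name the enroller among those unaware. If the enroller can learn past assignments, between about 9 and 16 of the 120 assignments can be known in advance, depending on whether the arm with the extra slot is known.

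The range rests on three assumptions: all earlier assignments in a block are seen, the block length is known, and blocks are 4:3:3 or a permutation of it. If past assignments are not seen, none of the 120 is certain. The documents do not show that selection bias will occur, and no size of bias in the treatment effect can be derived from them. That 10 does not divide by three is a separate matter; it enters here only through the assumed composition.

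**What to change.** In Section 2.3, replace the block length of 10 with permuted blocks whose size varies at random among multiples of three, for example 6, 9 and 12, and state that the sizes are not disclosed to site staff. In the same section, add the enrolling research assistant to those unaware of both past and upcoming assignments. The second change is essential, because varying sizes alone leave best guessing near 53% for someone who sees every earlier assignment.

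The cost is regenerating the list in the existing software and rewording one section. No extra patients or procedures are needed. The downside is a possible small imbalance in arm sizes if recruitment stops within a block.

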### Statistical analysis and power analysis

2.7

All analyses will be performed using SPSS for Windows, version 16, and GraphPad InStat. Analysis of variance is used for comparing mean values of patient's age, weight, height, and body mass index. For non-parametric measures like VAS and WOMAC, differences between baseline and post-treatment scores for each group are computed by the Wilcoxon signed ranks test. The difference between each treatment group is performed by the Kruskal–Wallis test. The level of statistical significance is set as *P* < .05. A power analysis is conducted to estimate the requisite sample size. From previous studies, a clinically significant difference reduction in the VAS was defined as 3 cm; a standard deviation of 3.49, probability of a Type I error of 0.05 and power of 0.8 resulted in an estimated sample size of 15. Consequently, a total of 120 subjects will be recruited.

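### Blocks of 10 do not divide among three arms: as written, no block can be balanced under 1:1:1 allocation, though the effect on the trial is modest

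*Protocol article*

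**What the plan says.** Section 2.3 (Random allocation) of the protocol article describes a computer-generated list made before the study starts and adds that "the randomization depends on random blocks of 10". The same paragraph names three arms: "Patients will be assigned at random to the ultrasound + LLLT group, LLLT group, or the ultrasound group". Section 2.7 (Statistical analysis and power analysis) sets the size: "a total of 120 subjects will be recruited". The Discussion repeats that total.

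No allocation ratio is stated anywhere, no second block size is given, and nothing says which arm takes the tenth place in a block. Section 2.3 points to Table 1 alongside the randomization sentence, but Table 1 is an empty baseline table and carries no allocation information.

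**The concern.** A permuted block delivers the planned ratio only if its size is a multiple of the sum of that ratio. For three equal arms the size must be a multiple of 3, and 10 is not. An unequal ratio summing to 10, such as 4:3:3, would fit, but none is stated, and a total that divides into 3 × 40 points to equal arms.

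This is more than detail left to a fuller document. The article fixes both the block size and the number of arms, and the two do not fit equal allocation. A fuller document could only supply an unequal ratio or a tenth-place rule, or show that the 10 is wrong.

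At stake is whether the list can be produced and audited from the text. Someone following section 2.3 must make an undocumented decision about the tenth place, and the final arm sizes depend on it.

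**Working it through.** A block size is a design choice, so there is no formula behind the 10 to reproduce. The check is whether it fits the rest of the design, and how much it matters if it does not.

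**Inputs.** From section 2.3: block size 10, three arms. From section 2.7: total 120, a VAS difference of 3 cm ("a clinically significant difference reduction in the VAS was defined as 3 cm"), "a standard deviation of 3.49", and "probability of a Type I error of 0.05 and power of 0.8". Assumptions: 1:1:1 allocation, each block as near equal as possible, and a two-sided 0.05 level (sidedness is not stated). The sample size of 15 in section 2.7 does not enter.

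**Step 1: divisibility.** 10 = 3 × 3 + 1, so the nearest split of a block is 4:3:3. 120/10 = 12 blocks and 120/3 = 40 per arm. Each block gives three places to every arm (12 × 3 = 36), and there are 12 extra places to distribute.

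**Step 2: final arm sizes under three rules for the extra place.**

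- Rotated through the arms: 36 + 4 each, giving 40/40/40.
- Always the same arm: 36 + 12, giving 48/36/36.
- Random in each block: the 12 extras are multinomial with probability 1/3 per arm. P(40/40/40) = 12!/(4!³ × 3¹²) = 34,650/531,441 = 0.065.

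Exact enumeration of the random case gives this distribution of largest minus smallest arm:

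| Difference | Probability | Cumulative |
|---|---|---|
| 0 | 0.065 | 0.065 |
| 2 | 0.313 | 0.378 |
| 3 | 0.198 | 0.576 |
| 4 | 0.157 | 0.733 |
| 5 | 0.152 | 0.885 |
| 6 or more | 0.115 | 1.000 |

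The median is 3 patients, the mean 3.4 and the 90th percentile 6.

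**Step 3: precision in the most unequal case (48/36/36).** The variance of a difference in means is proportional to 1/n₁ + 1/n₂.

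- 40 v 40: 1/40 + 1/40 = 0.0500.
- 36 v 36: 1/36 + 1/36 = 0.0556; ratio 1.11.
- 48 v 36: 1/48 + 1/36 = 0.0486; ratio 0.972.

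**Step 4: power.** Normal approximation, power = Φ(δ/(SD × √(1/n₁ + 1/n₂)) − 1.96), SD 3.49. The planned test is Kruskal–Wallis, so these figures are a guide to relative size only. The 2.19 cm row is an assumed smaller difference, chosen because 40 v 40 then has about 80% power.

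| Difference | 40 v 40 | 48 v 36 | 36 v 36 |
|---|---|---|---|
| 3 cm | 0.970 | 0.974 | 0.954 |
| 2.19 cm | 0.801 | 0.812 | 0.759 |

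**The case against.** The strongest reply is that little harm follows. Each completed 4:3:3 block keeps the arms within one patient of each other, so blocking still limits drift over calendar time. A rotating extra place returns exactly 40/40/40. Kruskal–Wallis does not need equal groups, and unequal arm sizes do not bias the comparison. In the 48/36/36 case only one of the three contrasts loses precision. If the larger arm were the combined group, both comparisons that bear on synergy would gain. At the article's own 3 cm, power stays at about 0.95 or more for every pair. All of this stands, and it limits the size of the point.

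A second reply is that 1:1:1 is nowhere stated and that a condensed article may leave the ratio and the tenth-place rule elsewhere. It stands as a caution: equal allocation is an inference from 120 = 3 × 40. It does not remove the point, because the figure that is printed fits equal arms only with a rule that is not printed, and an unequal ratio would itself need stating.

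A reader might infer more than the text supports:

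- That blocking is defeated, or that the trial will end unbalanced. Neither follows, because the result depends on an unstated rule and one natural rule gives exact balance.
- That the list could not be generated at all. The software is not named, so this cannot be shown.
- That the 10 was carried over from a two-arm design. The article offers no evidence on how the figure arose.

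**Conclusion.** The point holds in a limited form. Block size and number of arms are incompatible with equal allocation, and the article states neither a different ratio nor a way to place the tenth patient. That much is certain arithmetic. Under the assumed 1:1:1 ratio and near-equal blocks, the final sizes could lie anywhere from 40/40/40 to 48/36/36, with a typical gap of about 3 patients if the extra place is random.

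The effect on inference is small. The worst contrast has 11% more variance, which costs 1.6 percentage points of power at 3 cm (0.970 to 0.954) and about 4 points at 2.19 cm (0.801 to 0.759). This is a specification error that should be corrected because it is clear and cheap to correct, and not because it threatens the validity of the trial.

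**What to change.** State the 1:1:1 ratio in section 2.3 and replace 10 with block sizes that are multiples of 3 and fit 120. One suitable choice is blocks of 6 and 12 in random order, with the numbers of each fixed so that the list ends exactly at 120; for example, 8 × 6 + 6 × 12 = 48 + 72 = 120. This gives 40/40/40. If an unequal ratio was intended, state it. If blocks of 10 must stay, state the rule for the extra place.

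Randomly chosen blocks of 3, 6 and 9 cut off at 120 would be a weaker choice. With the three sizes equally likely, the list ends on a block boundary about half the time. Otherwise it stops after 3 of 6, 3 of 9 or 6 of 9 places, each with probability about 1/6. Those part-blocks are balanced with probability 8/20 = 0.40, 27/84 = 0.32 and 0.32. Exact balance therefore occurs in about 0.5 + (0.40 + 0.32 + 0.32)/6 = 0.67 of lists. Blocks of 3 also let the third assignment be deduced from the first two.

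The cost is regenerating the list, ideally before enrolment. If enrolment has begun, change from the next unused block. After k used blocks, 120 − 10k places remain, which is a multiple of 6 only when k is a multiple of 3. Otherwise the last block is cut short, and any inequality in the used blocks remains. Assignments near the end of a block keep a little predictability, less than with blocks of 3.

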### Secondary outcomes

2.6

Secondary outcome measures assessed are change in WOMAC score for pain stiffness and function, ROM, and muscle strength assessed at baseline and the end of the study. ROM and strength measurements are acquired by trained clinic staff on a small pilot cohort of sequentially enrolled patients using computerized dual inclinometry ROM and muscle tester equipment (JTECH Medical, Midvale, UT). To assess ROM, 1 inclinometer is positioned on the quadricep muscle at mid femur and the other at mid-tibia. Patients are asked to lay flat on their back and lift their leg and flex at the knee to measure flexion. Patients are then asked to sit at the edge of the table and extend their leg to measure extension. To assess muscle strength, a manual muscle tester is used. Patients are asked to sit at the edge of the table with their knee at approximately 90 degrees. The manual muscle tester is positioned and hold at anterior mid tibia while patients are asked to extend their leg to measure extension strength. To measure flexion strength, the muscle tester is held at anterior mid-tibia and the patient is asked to flex at the knee. Each ROM and muscle strength test is repeated 3 times and the average is recorded (Table 2).

**Table 2 T2:** Postoperative outcomes.

Outcomes	Combined group	LLLT group	Ultrasound group	*P* value
VAS				
WOMAC				
ROM				
Muscle strength				

LLLT = low-level laser therapy, ROM = range of motion, VAS = visual analog scale, WOMAC = Western Ontario and McMaster Universities Osteoarthritis Index.

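### The three active arms can show whether the combination beats each modality alone, but not the synergy that the protocol sets out to evaluate

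*Protocol article*

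**What the plan says.** The Introduction of the protocol article gives the purpose as "to evaluate the synergistic effects of simultaneously applying ultrasound plus LLLT on pain and muscle function in patients with knee osteoarthritis". The Abstract (Background) and the Discussion say the same. All three present the trial as the larger study needed to confirm a synergy examined before in one small study.

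Section 2.3 (Random allocation) fixes the arms: "Patients will be assigned at random to the ultrasound + LLLT group, LLLT group, or the ultrasound group". The shell of Table 2 has the columns "Combined group LLLT group Ultrasound group", and Table 1 has the same three. Section 2.4 describes active laser and active ultrasound only. No untreated, sham or placebo arm appears. Figure 1 is not available, but the text and both tables agree on three arms.

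The hypothesis, in the Introduction, the Discussion and the Abstract (Conclusion), is that "there will be a remarkable difference in postoperative outcomes between the intervention and control groups". Section 2.2 says: "The study protocol is a randomized, controlled, double-blind design". No arm is named as the control.

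For the comparison between arms, section 2.7 says: "The difference between each treatment group is performed by the Kruskal–Wallis test".

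**The concern.** The aim, the arms and the stated test do not address the same question. In a trial of a combination, synergy ordinarily means that the joint effect exceeds the sum of the two separate effects. Each separate effect is measured against neither treatment, and this trial does not observe that state. A combined arm that does better than both single arms would be compatible with effects that add up exactly, fall short of adding up, or exceed it.

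The hypothesis does not settle what is compared, because it does not say which arms are the controls. The omnibus test does not settle it either, since it responds to any difference among the three arms.

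What is at stake is the conclusion. With the aim as written, a favourable result would naturally be reported as confirmed synergy, and no analysis of these data could support or refute that.

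**Working it through.** **Inputs.** The arms come from section 2.3. The 3 cm VAS difference, SD of 3.49, type I error of 0.05, power of 0.8 and total of 120 come from section 2.7. The protocol gives no figure for an interaction and none for the change expected without treatment, so the arm means below are assumptions. The sample-size figure of 15 in section 2.7 plays no part, because the point holds at any N.

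**Step 1: the contrast.** Let M be the mean VAS reduction. Synergy on this scale is

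(M_both − M_neither) − [(M_LLLT − M_neither) + (M_US − M_neither)] = M_both − M_LLLT − M_US + M_neither.

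**Step 2: is it estimable?** Write each arm as a row of coefficients for (baseline, LLLT, ultrasound, interaction):

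- combined: (1, 1, 1, 1)
- LLLT: (1, 1, 0, 0)
- ultrasound: (1, 0, 1, 0)

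To isolate the interaction, (0, 0, 0, 1), the fourth column forces a weight of 1 on the combined arm. The second and third columns then force −1 on LLLT and −1 on ultrasound. The first column becomes 1 − 1 − 1 = −1, not the 0 required. So the contrast cannot be formed: the design has rank 3 for 4 parameters. A neither-treatment row, (1, 0, 0, 0), raises the rank to 4 and makes it estimable.

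**Step 3: what this means in centimetres.** Assume reductions of 4.5 (combined), 3 (LLLT) and 3 (ultrasound). The interaction is 4.5 − 3 − 3 + M_neither = −1.5 + M_neither.

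| Assumed M_neither (cm) | Interaction (cm) | Reading |
|---|---|---|
| 1.0 | −0.5 | sub-additive |
| 1.5 | 0 | additive |
| 2.0 | +0.5 | super-additive |

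In every row the observed arms are identical, and the combination beats each component by 1.5 cm.

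**Step 4: what the stated test answers.** Kruskal–Wallis tests whether the three distributions are the same. Suppose the reductions were 4 (combined), 4 (LLLT) and 1 (ultrasound), again assumed. The test could reject because ultrasound lags by 3 cm, although the combination adds nothing to LLLT.

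**Step 5: what three arms can answer.** Combined versus LLLT and combined versus ultrasound are both estimable. Assume equal allocation, 120/3 = 40 per arm, since the ratio is not stated, and a two-sided 0.05 test by normal approximation:

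- SE = 3.49 × √(2/40) = 0.780 cm.
- For a 3 cm difference: 3/0.780 = 3.84; 3.84 − 1.96 = 1.88; power about 97% per contrast.
- If both must succeed and both true differences are 3 cm, joint power is at least 1 − 2 × 0.03 = 94%.
- For a 1.5 cm difference, as in Step 3: 1.5/0.780 = 1.92; 1.92 − 1.96 = −0.04; power about 48%.

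**The case against.** The best defence is that the article never defines synergy as a departure from additivity and states no interaction hypothesis. The word may mean only that the combination works better than either modality alone, with the single-modality arms as the controls. Three arms are enough for that question. This stands as a description of what the design can do, but the article nowhere says it. If it is what was meant, it is the restatement recommended below, and the present wording still invites the stronger claim.

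A second defence is that pairwise tests may stand in a fuller plan that is not shown. That is possible, and their absence from the article is not held against it. The point is narrower: the test that is stated does not answer the question that is stated.

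Third, the example uses assumed means and takes raw VAS change as the additive scale. That is so. It shows that the sign is undetermined, not that an error of known size exists. Outside assumptions can bound the answer. If M_neither is taken to lie between 0 and 3 cm in Step 3, the interaction lies between −1.5 and +1.5 cm. Such a bound comes from the assumption and still leaves the sign open.

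A reader might also infer that the trial has no control group. The documents do not support that, because the single-modality arms can serve as active controls. The defect is that they are not named as such.

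**Conclusion.** The point holds: the objective is wrong as written for this design. Synergy beyond additivity is not estimable from combined, LLLT and ultrasound arms at any sample size. This rests only on the arms in section 2.3 and on the ordinary additive meaning of synergy. The ±0.5 cm example rests on assumed means and on raw VAS change as the scale.

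Two stronger inferences should be resisted. A reader might conclude that the trial cannot support any useful finding. It can: a randomised comparison of the combination with each component is sound, and at an assumed 40 per arm it has about 97% power per contrast for 3 cm. A reader might also call the −0.5 cm case antagonistic. Sub-additive is the right term, because the combination still beats each component.

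The reference to postoperative outcomes in a trial with no operation is a separate clerical slip and adds no weight here.

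**What to change.** **Objective and hypothesis** (Abstract Background and Conclusion, Introduction, Discussion). Restate them as added benefit: whether ultrasound plus LLLT gives a better result than LLLT alone and than ultrasound alone. Name those two arms as the active comparators. Make no claim of synergy, and state as a limitation that additivity and synergy cannot be separated without a neither-treatment or sham arm.

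**Analysis** (section 2.7). Pre-specify combined versus LLLT and combined versus ultrasound as the between-group tests, for example as rank-sum tests on change from baseline. State the success rule:

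- If both contrasts must be significant, each can be tested at 0.05 with no adjustment.
- If either one suffices, a multiplicity adjustment is needed.

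Kruskal–Wallis may remain as a supporting overall test.

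**Cost.** A less ambitious claim and slightly more analysis, with no added arm or patients.

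**If the sponsor wants to keep the synergy claim**, a fourth arm and a pre-specified interaction contrast would be needed. With 120 patients over four arms (30 each), SE = 3.49 × √(4/30) = 1.27 cm, and power for an assumed 3 cm interaction is about 65%. For 80% power, 4 × [3.49 × (1.96 + 0.84)/3]² rounds up to 43 per arm, or 172 in all. Smaller interactions would need more.
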